#### Instrument

The measurement tool will be similar to the final version of questionnaire, which will be designed based on the matrix (change, determinants, and practical objectives). The questionnaire will consist of two parts as follows: demographic information, and change objectives and expected outcomes of the program. The validity and reliability of the questions will be examined by the opinions of a number of experienced experts in this field.

*The measurement of primary outcomes* (1) level of hookah cessation immediately after the intervention, (2) level of hookah cessation within 3 months of the intervention, (3) level of hookah cessation within 6 months of the intervention, and (4) level of hookah cessation within 9 months of the intervention.

*The measurement of secondary outcomes* (1) Comparison of the frequency of hookah consumption before and after the intervention for those who did not stop hookah smoking, (2) point prevalence of study participants (no hookah use during the past 7 days) at the end of the intervention and at 3, 6 and 12 month follow-up, (3) comparison of the number of hookah cessation attempts before and after the intervention, (4) participants’ tendency to stop hookah 6 months after the intervention, (5) rate of cessation as a result of intervention among the study participants after 6 months, and (6) rate of cessation as a result of intervention among the study participants after 12 months.

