#### Sample size

To calculate the sample size in this semi-experimental study, the sampling formula in comparative studies will be used, considering (d = 1, s1 = 2.55 and s2 = 2.38, respectively) based on the findings of similar studies (self-efficacy three months after training in both intervention and control groups in the study of Ahmed Sotoudeh), [26]. Also, considering the errors of α = 0.05 and β = 0.2 (power of 80%), the sample size will be calculated as 96 individuals in each group. However, by taking 10% sample drop into account, the number of samples in each group will be estimated as 106 individuals.

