#### Statistical analysis

After data collection, the data will be analyzed by SPSS-19 software using descriptive statistics (frequency and percentage, mean and standard deviation), independent and paired t-test, path analysis, and logistic regression analysis. The p < 0.05 will be considered as statistically significant.

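### Cessation at four time points is primary with none named as decisive; if any one result at p < 0.05 counts as success, the type I error exceeds its nominal level

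*Protocol article*

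**What the plan says.** All references are to Step 6 of the protocol article.

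- **Instrument.** Four outcomes are listed as primary: "1) level of hookah cessation immediately after the intervention, (2) level of hookah cessation within 3 months of the intervention", then "3) level of hookah cessation within 6 months of the intervention, and (4) level of hookah cessation within 9 months of the intervention". None is marked as the main one.
- **Statistical analysis.** The methods named are "independent and paired t-test, path analysis, and logistic regression analysis", followed by one general rule: "The p < 0.05 will be considered as statistically significant". No test is tied to a particular primary outcome. No order of testing, split of alpha, joint test over time or rule for combining the four results is given.
- **Sample size.** A single comparison of means is used, with 5% type I error and 80% power: "the sample size will be calculated as 96 individuals in each group", raised to 106 for dropout. The variable is a self-efficacy score, not cessation.
- **Timing.** The text under Exclusion criteria schedules a pretest and assessments 3, 6 and 12 months after training starts. Duration of the intervention describes 3 months of recruitment and training, then 12 months of follow-up.

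**The concern.** Cessation just after training and cessation 9 months later answer different questions, yet both have equal standing as primary. With one general threshold and no decisive time point, a difference seen only at the end of training could be reported as a positive primary result even if nothing remained at the last follow-up. Each extra chance of success also raises the probability of at least one false positive above the level of a single test. Outcomes are self-reported without biochemical validation (Strengths and limitations), which is a further reason to settle the decisive time point in advance.

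**Working it through.** **1. The plan's own figure.** Inputs from Sample size: difference 1, SDs 2.55 and 2.38, alpha 0.05, power 80%. Sidedness is not stated.

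n per group = (z₀.₉₇₅ + z₀.₈₀)² × (s₁² + s₂²) / d² = (1.960 + 0.842)² × (6.5025 + 5.6644) / 1² = 95.5, rounded up to 96.

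This matches the stated 96. A one-sided test would give 76, so the stated figure is two-sided. For dropout, 96 × 1.10 = 105.6, which rounds to the stated 106; dividing by 0.9 would give 107. The calculation therefore covers one two-sided test at 0.05, on a self-efficacy mean.

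**2. Error over several primary tests.** Assumptions not in the article: each time point is tested separately at two-sided 0.05, any one significant result counts as success, and no true effect exists at any time point.

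- Four independent tests: 1 − 0.95⁴ = 18.5%.
- Three independent tests: 1 − 0.95³ = 14.3%.
- Four independent tests, false results favouring the intervention only: 1 − 0.975⁴ = 9.6%, against a nominal 2.5%.

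The four results are repeated reports by the same women, so the test statistics will be positively correlated. The article gives no correlation, so a range is shown, from simulation of four equally correlated normal test statistics (1,000,000 draws per setting):

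| Assumed correlation | At least one p < 0.05, either direction | In favour of the intervention only |
|---|---|---|
| 0.5 | 15.6% | 7.8% |
| 0.7 | 13.0% | 6.5% |
| 0.8 | 11.4% | 5.7% |
| 0.9 | 9.3% | 4.7% |
| 0.95 | 8.0% | 4.0% |
| 1 | 5.0% | 2.5% |

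If correlation instead decays with the gap between time points (first-order autoregressive), the two-sided figures are 16.6% at 0.5, 12.6% at 0.8 and 10.3% at 0.9.

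**3. How many time points are assessed.** If each woman's training lasts 3 months, visits at 3, 6 and 12 months from its start fall 0, 3 and 9 months after its end. The 6-month primary outcome then has no scheduled visit, and the three-test figure is the relevant upper limit.

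**4. What adjustment would cost.** Bonferroni over four tests each at 0.05/4 = 0.0125. The family-wise error is then 1 − 0.9875⁴ = 4.9% if independent, and at most 5% under any correlation. On the article's inputs, n = (2.498 + 0.842)² × 12.1669 = 136 per group after rounding up, or 136/0.9 = 152 with dropout. At 96 per group, power per test would be about 62%. These figures only illustrate the cost, because the inputs describe self-efficacy.

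**The case against.** The strongest objection is that the error figures rest on a decision rule the article never states. It gives a general threshold for a list of methods. It does not say that four separate between-group tests will be run, or that any one of them suffices. A rule requiring success at all four would not inflate the error. Adjustment methods are also commonly left to a statistical analysis plan, which is not shown. This stands as far as it goes: the inflation is conditional, and the absence of a named adjustment is not in itself a fault. But the article does fix four co-equal primary time points with none decisive, and it states no all-four rule.

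A reader might infer that the chance of a false claim of effectiveness is well above 5%, or that it is 18.5%. The article does not support either. The 18.5% needs independence, which is implausible for repeated reports of one behaviour; the primary outcomes' wording could even be read as overlapping windows, which would raise the correlation. A false claim of effectiveness is an error in one direction, about 5% to 8% at correlations of 0.9 to 0.5. The benchmark for that is 2.5%, so it is still roughly two to three times nominal.

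Nor does the sample-size section show how alpha is spent on cessation, since it concerns another variable. Nothing in the article shows that an effect is easier to obtain just after training.

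**Conclusion.** The point holds in a limited form. The article names four primary time points for cessation, none decisive, alongside one general 0.05 threshold. If each is tested at that level and any one success suffices, the two-sided family-wise error is about 9% to 16% at assumed equal correlations of 0.9 to 0.5. In the favourable direction alone it is about two to three times the nominal 2.5%. The inflation disappears only at correlation 1 or under a stricter success rule, and neither is stated. Because the decision rule is inferred, the firm part of the finding is the missing decisive time point; the size of the inflation is conditional.

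**What to change.** First reconcile the timing given under Exclusion criteria, Instrument and Duration of the intervention, so that it is clear which post-intervention time points are assessed and whether they are counted from the start or the end of training. Then name one assessed time point as the single primary outcome and make the others secondary. That restores a 5% error for the primary test and leaves 96 per group unchanged on the article's own inputs.

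If several time points must stay primary, either test them in a fixed order beginning with the decisive one, each at 0.05 and stopping at the first non-significant result, or use Holm at a family-wise 0.05.

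The multiplicity problem does not require a new definition of cessation. Substituting the 7-day point prevalence now listed as secondary would be a separate decision. Choosing simply the last visit would also run into the unresolved difference between 9 months in the primary list and 12 months elsewhere.

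The cost of a single primary is a change of wording in the protocol and registry. The sponsor gives up the option of claiming success from whichever time point turns out favourable. Holm would lower power per test: its first step uses 0.0125, where power is about 62% at 96 per group on the self-efficacy inputs.

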#### Exclusion criteria

Simultaneous use of cigarettes and other tobacco products or drugs, and being absent in more than 20% of the training sessions are among the exclusion criteria.

With regard to the research objectives set out in the previous steps, appropriate training strategies and activities will be selected for the intervention group, and later on, the types of anticipated activities will be introduced to the samples in intervention group in terms of the scheduled program. Then, the training intervention will be implemented based on the previous steps. The number of sessions, duration of each session and intervention, and number of participant in each intervention session will be determined by the research team according to the needs of intervention group. The assessment will be performed based on a pretest that will be taken before the beginning of the intervention, as well as 3، 6, and 12 months after the start of training program.

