#### Duration of the intervention

The implementation phase of intervention will be completed in a duration of 12 months. The women will be recruited and trained for a period of 3 months, and will receive followed up for another 12 months.

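### The assessment schedule, the primary cessation time points and the follow-up period use different clocks, and the stated schedule leaves at least one primary outcome without a matching assessment

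*Protocol article*

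**What the plan says.** Three sections of the protocol article bear on this.

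- **Exclusion criteria, closing paragraph.** This holds the general assessment schedule: a pretest, then assessments at 3, "6, and 12 months after the start of training program". The clock starts when training starts. The same paragraph leaves the length of the intervention to the research team.
- **Instrument, primary outcomes.** There are four: "level of hookah cessation immediately after the intervention", "level of hookah cessation within 3 months of the intervention", "level of hookah cessation within 6 months of the intervention" and "level of hookah cessation within 9 months of the intervention". The reference point is the intervention, and the first item suggests its end.
- **Instrument, secondary outcomes.** Seven-day point prevalence is to be taken "at the end of the intervention and at 3, 6 and 12 month follow-up". Secondary outcome 4 is set 6 months after the intervention. Outcomes 5 and 6 are cessation rates after 6 and 12 months, with no origin given.
- **Duration of the intervention.** "The women will be recruited and trained for a period of 3 months, and will receive followed up for another 12 months". The section also says: "The implementation phase of intervention will be completed in a duration of 12 months".

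**The concern.** The schedule counts from the start of training, while the primary outcomes appear to count from the end of the intervention. The primary list has a 9-month point that appears in no schedule. The secondary list has a 12-month point that the primary list lacks.

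Step 6 names cessation or reduction as the purpose of the evaluation. The limitations section says smoking status will not be confirmed biochemically. A time point without a contact therefore has no alternative measure described in the article.

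The mixed clocks also make labels ambiguous. With a 3-month training, the assessment at start+12 is the 12-month visit on one clock and the 9-month visit on the other. Unless the protocol says which, two analysts could report different primary results from the same data.

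**Working it through.** The article gives no computed figure on this point, so the check sets the stated times side by side.

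**Inputs**
- Scheduled assessments, in months from the start of training: 3, 6, 12 (Exclusion criteria section).
- Length of training: D months. The article does not fix it. D = 3 is an assumption suggested by the Duration section, where the 3 months also include recruitment.
- Primary outcomes counted from the end of training fall at D, D+3, D+6 and D+9 (Instrument section).
- A match is allowed if an assessment lies within half a month of the required time. This tolerance is mine.

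**Counting argument.** The four times are 3 months apart, so no single assessment can serve two of them. Three assessments can match at most three, and at least one primary is unmatched for every D.

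**Clock from the end of training, against 3, 6 and 12**

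| D (months) | Times needed | Primaries with no match |
|---|---|---|
| 1 | 1, 4, 7, 10 | all four |
| 2 | 2, 5, 8, 11 | all four |
| 3 | 3, 6, 9, 12 | 6-month |
| 6 | 6, 9, 12, 15 | 3-month and 9-month |
| 12 | 12, 15, 18, 21 | 3-, 6- and 9-month |

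With D varied from 0 to 12 months in steps of 0.05, the smallest number of unmatched primaries is 1.

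**Clock from the start of training.** The primaries fall at D, 3, 6 and 9. Month 9 is not scheduled, so the 9-month primary is unmatched. The end-of-training primary (D) has its own assessment only if D is close to a scheduled month. At D = 3 it is the same assessment as the 3-month primary.

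**Times in the secondary outcome list used as the schedule.** Assessments at D, D+3, D+6 and D+12 do not include D+9, so the 9-month primary is again unmatched.

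**Both schedules carried out together.** The 9-month primary needs D+9 to be one of 3, 6, 12, D, D+3, D+6 or D+12. For a non-negative D, only D+9 = 12 works, so D = 3. Assessments then fall at 3, 6, 9, 12 and 15, and all four primaries are covered. At D = 1, 2, 4 or 6 the 9-month primary is still unmatched.

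**Twelve-month follow-up.** Counted from the end of training, it falls at D+12. With D = 3 this is 3 + 12 = 15 months from the start, against a last scheduled assessment at 12. The 6-month secondary outcome on the same clock falls at 3 + 6 = 9, also unscheduled.

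**The case against.** The strongest reply is that the Instrument section states measurement times of its own and the Duration section promises 12 further months of follow-up, so the schedule under Exclusion criteria need not be the only one. If both are carried out and training lasts exactly 3 months, every primary is covered. A reader might infer that a primary outcome lacks data on any reading. That goes too far, because this combined reading works. But no section states a combined schedule, and it depends on a training length that the article leaves open.

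A reader might also infer that cessation 12 months after training is never measured. The documents do not support that. The Instrument and Duration sections both mention 12 months of follow-up; they conflict with the schedule under Exclusion criteria, and the article does not say which prevails.

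It is tempting to set 3 + 12 = 15 months against the 12 months in the Duration section as an arithmetic contradiction. The 12 months there describe an implementation phase, which is not said to be the whole study. The wording is unclear, but no contradiction is shown.

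Finally, cessation within 9 months could mean a cumulative period, partly recoverable from earlier visits or by recall at 12 months. That is possible, and for this reason I say no matching assessment rather than no data. The article describes no such recall or derivation.

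Nothing in the text suggests that anyone intends to relabel visits after seeing results. The ambiguity merely leaves that open.

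**Conclusion.** The point holds as an internal inconsistency in time origin and assessment times across the three sections. Under the schedule in the Exclusion criteria section, at least one of the four primary outcomes has no matching assessment, whatever the training length. Which one depends on the clock: the 6-month primary (start+9) from the end of an assumed 3-month training, or the 9-month primary from the start. At D = 3, the 9-month primary on the end-of-training clock falls at start+12 and is assessed, so the two clocks do not lose the same outcome. Training of 1 or 2 months matches worse on the end-of-training clock.

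The 12-month follow-up conflicts with the schedule only if it is counted from the end of training.

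The result rests on the stated times, the half-month tolerance, and reading each primary as a status at a time point. It should be settled before follow-up begins, because a contact not made then may not be recoverable later.

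**What to change.** Choose one time origin and one list of assessment times, and use them in the schedule under Exclusion criteria, the outcome lists under Instrument, and the Duration section. State the length of training, or write the times in terms of it. Then take one of two routes.

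1. **Keep the scheduled assessments.** Restate the primary and secondary time points so that each falls on one of them. This must include the end-of-intervention primary, which has no visit of its own if training is clearly shorter than 3 months and duplicates the 3-month outcome if training lasts exactly 3. Replacing the 9-month primary alone is therefore not enough.
2. **Keep the end-of-training clock.** Add the missing questionnaire contacts. With a 3-month training these are start+9, and start+15 if 12 months after training is intended. With another length the list must be worked out again.

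Either way, give secondary outcomes 5 and 6 an explicit origin, say whether within 3, 6 or 9 months means status at that time or cessation over the period, and say what the 12-month implementation phase covers.

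Route 1 costs protocol and registry wording. Route 2 costs the same wording plus one or two extra questionnaire contacts per participant, assuming a 3-month training.

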#### Duration of the intervention

The implementation phase of intervention will be completed in a duration of 12 months. The women will be recruited and trained for a period of 3 months, and will receive followed up for another 12 months.

#### Statistical analysis

After data collection, the data will be analyzed by SPSS-19 software using descriptive statistics (frequency and percentage, mean and standard deviation), independent and paired t-test, path analysis, and logistic regression analysis. The p < 0.05 will be considered as statistically significant.

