#### Recruitment

The random method will be used for sampling. First, four comprehensive health centers will be randomly selected in Bandar Abbas, from which, two will be randomly assigned to the intervention group and two to the control group. The number of samples from each center will be determined according to the population covered by the center. To select eligible individuals, SD will randomly select a family record belonging to the population covered by the selected comprehensive health centers.

Then, to select other people, the researcher will visit all houses on the right side of the first selected record. After identifying the samples and obtaining informed consent from them, the phone number of all samples will be obtained for correspondence.

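### Whole health centres are allocated, two per arm, but the between-arm tests and the sample size treat women as independently allocated; false positives exceed 5% by an amount that depends on an intracluster correlation the protocol does not give

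*Protocol article*

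**What the plan says.** - **Allocation (Recruitment).** The protocol article states that "four comprehensive health centers will be randomly selected in Bandar Abbas" and that "two will be randomly assigned to the intervention group and two to the control group". Within a centre, one family record is drawn at random and further women are found by visiting neighbouring houses. On numbers per centre: "The number of samples from each center will be determined according to the population covered by the center".
- **Sample size (Sample size).** The inputs are "d = 1, s1 = 2.55 and s2 = 2.38, respectively", taken from self-efficacy three months after training in an earlier study, with α 0.05 and 80% power. The result is that "the sample size will be calculated as 96 individuals in each group", raised to 106 for 10% loss.
- **Analysis (Statistical analysis).** After descriptive statistics, the methods listed are "independent and paired t-test, path analysis, and logistic regression analysis", and p below 0.05 "will be considered as statistically significant".

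The article nowhere mentions an ICC, a design effect, a mixed model, GEE, cluster-robust standard errors or a centre-level comparison.

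**The concern.** The centre is the unit that is allocated, so the comparison of arms rests on four units. An ordinary independent t-test or logistic regression, or a path model that includes arm, takes its standard error from variation between women and assumes that each woman was allocated on her own. If women from the same centre resemble one another, that standard error is too small. A chance difference between one pair of centres and the other could then be reported as an effect of the programme. Step 6 gives the effectiveness of the programme as the purpose of this evaluation, so the main claim is at stake.

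Some resemblance is plausible. Women are recruited from neighbouring houses, and the programme is delivered in sessions whose group size is still to be decided.

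**Working it through.** **1. Reproduce the plan's sample size.** Inputs from Sample size: difference 1, SDs 2.55 and 2.38, α 0.05 (taken as two-sided), power 80%.

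n per group = (1.960 + 0.842)² × (2.55² + 2.38²) / 1² = 7.849 × 12.167 = 95.5, rounded up to 96. Then 96 × 1.1 = 105.6, rounded to 106. The plain individual-level formula reproduces both figures, so there is no allowance for clustering in them.

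**2. Women per centre.** Two centres per arm give an average of 96/2 = 48 evaluable or 106/2 = 53 enrolled women. Actual sizes will differ, because they follow the population covered.

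**3. False-positive rate of the unadjusted between-arm test.** Design effect DE = 1 + (m − 1) × ICC. True rate at nominal 5% = 2 × [1 − Φ(1.96/√DE)]. The ICC is an assumption throughout.

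| Assumed ICC | DE, m = 48 | True rate | DE, m = 53 | True rate |
|---|---|---|---|---|
| 0.001 | 1.047 | 5.5% | 1.052 | 5.6% |
| 0.005 | 1.235 | 7.8% | 1.26 | 8.1% |
| 0.01 | 1.47 | 10.6% | 1.52 | 11.2% |
| 0.02 | 1.94 | 15.9% | 2.04 | 17.0% |
| 0.05 | 3.35 | 28.4% | 3.60 | 30.2% |
| 0.10 | 5.70 | 41.2% | 6.20 | 43.1% |

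Simulation (20,000 trials per setting, no effect, two against two centres of 53) agrees. The t-test rejected in 11.6%, 17.2% and 30.9% of trials at ICC 0.01, 0.02 and 0.05. Logistic regression, with cessation rates of 10–30%, rejected in 9.9–11.0% at ICC 0.01 and 27–30% at 0.05. A t-test on the four centre means held about 5%.

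**4. Power of a valid centre-level test.** Four centres leave 2 degrees of freedom, so the critical t is 4.30 instead of 1.96. With pooled SD √(12.167/2) = 2.466 and 96 evaluable per arm, SE = 2.466 × √(2 × DE/96), and power follows from the noncentral t with noncentrality 1/SE.

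| Assumed ICC | SE | Noncentrality | Power |
|---|---|---|---|
| 0 | 0.356 | 2.81 | 35% |
| 0.01 | 0.432 | 2.32 | 27% |
| 0.02 | 0.496 | 2.02 | 22% |
| 0.05 | 0.652 | 1.53 | 15% |

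At ICC 0.01 the expected 95% CI half-width is roughly 4.30 × 0.432 = 1.86, against 1.96 × 0.356 = 0.70 for the unadjusted analysis.

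**5. The same women in more centres.** With 96 evaluable per arm spread over six centres per arm (16 each, 10 degrees of freedom), power is about 66%, 60% and 48% at ICC 0.01, 0.02 and 0.05. With twelve per arm it is about 74%, 71% and 64%.

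**The case against.** **The article is condensed.** Its analysis section is a short list of methods, and the error structure of the regression could be set out in a plan that is not shown. This carries limited weight. An ordinary independent t-test and a threshold are expressly named, and the sample size shows that the plan works with individual women as the unit. Calling the evaluation quasi-experimental tempers the causal claim but does not correct the standard errors.

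**The size of the error is not known.** This stands. A reader might infer that false positives will be two to six times the stated 5%. The document does not support that as a fact. The multiple holds only for an ICC of roughly 0.01 to 0.05; it is about 1.1 at 0.001, 1.6 at 0.005 and over 8 at 0.10. Adjustment for the pretest could lower it, while unequal centre sizes and next-door recruitment would tend to raise it. That women in a centre share staff or social circles is inference.

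**The list of methods is wider than the problem.** This also stands. A reader might take the whole list to be at fault, but the paired t-test is a before-after comparison within an arm, and the rates above do not describe it.

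**The number per centre is not fixed.** A reader might also take 53 women per centre as planned. It is only an average of enrolled women; the evaluable average is 48. The range shown covers both, and the conclusion is the same.

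**Conclusion.** The mismatch is real as written: centres are allocated, whereas the between-arm tests and the sample size use women as independent units, and nothing elsewhere in the article corrects this. At nominal 5%, the true false-positive rate runs from about 5.5% to 43% as the assumed ICC goes from 0.001 to 0.10, and is about 11% to 30% for an ICC of 0.01 to 0.05. These figures assume equal centre sizes of 48 or 53 and no covariate adjustment.

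The stated 80% power does not hold for this design even at ICC 0, because 2 degrees of freedom alone reduce it to about 35%. A reader might infer that dividing the same women among more centres would put this right. It would help, but none of the spreads examined reaches 80%.

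**What to change.** **Statistical analysis section.** Make the main between-arm analysis one that respects the centre as the unit. The preferred form is one pretest-adjusted summary per centre (adjustment made at the level of the woman), compared between arms by a t-test on 2 degrees of freedom. A model with a centre random intercept is fragile with four centres and acceptable only with between-cluster degrees of freedom. Report the estimate with its cluster-based 95% CI, and state that the four-centre comparison between arms is exploratory. The paired t-test may stay as a within-arm description.

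**Sample size section.** State an assumed ICC with a range, and restate the power for 96 evaluable women per arm: about 35%, 27%, 22% and 15% at ICC 0, 0.01, 0.02 and 0.05.

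**Cost.** The changes are to wording and some programming. The real price is a much wider interval and a far less favourable stated power. Spreading the same women over more centres before allocation is optional: it raises power to the values in step 5 of the working, needs more training venues, and is not part of the minimum correction.

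### For measures taken at the pretest, the only mean comparisons named are independent and paired t-tests; a baseline-adjusted between-arm model would serve them better at almost no cost

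*Protocol article*

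**What the plan says.** All references are to Step 6 of the protocol article.

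- **Statistical analysis** gives the inferential methods as "independent and paired t-test, path analysis, and logistic regression analysis", after descriptive statistics. It ties no method to an outcome and names no baseline covariate, analysis of covariance (ANCOVA), mixed model or centre term.
- **Exclusion criteria**, which also holds the assessment schedule, says: "The assessment will be performed based on a pretest that will be taken before the beginning of the intervention". Follow-up is at 3, 6 and 12 months.
- **Recruitment** draws four health centres at random, of which "two will be randomly assigned to the intervention group and two to the control group".
- **Instrument** makes cessation the primary outcome. Two secondary outcomes are framed as before/after contrasts: consumption frequency among women who did not stop, and "comparison of the number of hookah cessation attempts before and after the intervention".
- **Inclusion criteria** admits only women who already smoke hookah regularly.
- **Sample size** rests on a comparison of two mean self-efficacy scores with no use of the pretest ("d = 1, s1 = 2.55 and s2 = 2.38, respectively").

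**The concern.** The stated purpose of Step 6 is to evaluate the programme's effect, which needs a contrast between arms. Neither named t-test makes good use of the pretest for that.

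The paired t-test looks at change within one arm. Any general time trend is counted in that change. So is regression to the mean, which is to be expected when women are selected on how often they smoke. A significant paired result in the intervention arm would not show that the programme worked.

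The independent t-test does compare arms. Applied to follow-up values, however, it leaves part of any baseline difference in the estimate and forgoes the variance that the pretest could explain. With only two centres per arm, randomisation gives limited protection against baseline differences.

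**Working it through.** **1. Reproduce the plan's figure.** From Sample size: d = 1, s1 = 2.55, s2 = 2.38, α = 0.05, power 80%. Sidedness is not stated; two-sided is the reading that reproduces.

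- Common SD = √((2.55² + 2.38²)/2) = √6.083 = 2.466, so the target is 1/2.466 = 0.405 SD.
- n per arm = (2.55² + 2.38²)(1.96 + 0.842)²/1² = 95.5, rounded up to 96. A one-sided test would give 76.
- Adding 10%: 96 × 1.10 = 105.6, which gives 106.

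The article's statements "the sample size will be calculated as 96 individuals in each group" and "the number of samples in each group will be estimated as 106 individuals" are both reproduced. They correspond to an unadjusted two-sample comparison with 80.2% power (79.8% from the t distribution).

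**2. Precision given up.** The article gives no pretest-to-follow-up correlation, so rho is assumed at 0.3, 0.5 and 0.7. ANCOVA multiplies the SD by √(1 − rho²); a t-test on change scores multiplies it by √(2(1 − rho)). Power is at 96 per arm by the normal approximation, **ignoring clustering**.

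| rho | Variance ratio, unadjusted to ANCOVA: 1/(1 − rho²) | ANCOVA power | ANCOVA n per arm | Change-score power |
|---|---|---|---|---|
| 0.3 | 1/0.91 = 1.10 | 83.8% | 87 | 66.1% |
| 0.5 | 1/0.75 = 1.33 | 90.0% | 72 | 80.2% |
| 0.7 | 1/0.51 = 1.96 | 97.6% | 49 | 95.2% |

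The unadjusted comparator is 80.2% power and 96 per arm.

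**3. Size of chance imbalance.** Assume two centres of 48 per arm, a pretest SD of 2.466, and a range for the intracluster correlation (ICC), which the article does not give. The SD of the baseline difference between arms is 2.466 × √(2 × (ICC/2 + (1 − ICC)/96)). On the score scale, against a target of 1:

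| ICC | SD of baseline difference | Probability it exceeds 0.5 either way | SD carried into follow-up at rho = 0.5 |
|---|---|---|---|
| 0 | 0.356 | 16% | 0.178 |
| 0.01 | 0.432 | 25% | 0.216 |
| 0.05 | 0.652 | 44% | 0.326 |

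The last column is rho times the second. The ICC = 0 row is ordinary sampling error, present in any individually randomised trial of this size. Only the excess over it comes from allocating centres.

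**4. What adjustment does not reach.** With 48 per centre the design effect is 1 + 47 × ICC, that is 1.47 at ICC 0.01 and 3.35 at 0.05. Unadjusted power, at an effective n of 96 divided by the design effect, falls from 80% to about 64% and 34%. That is before any loss from having only two degrees of freedom between centres. The powers in step 2 are therefore not what this trial would attain.

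**The case against.** A reader might infer that the trial compares its arms, primary outcome included, only by unadjusted t-tests, and that baseline imbalance passes whole into the effect estimate. The documents do not support that reading, for these reasons.

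- The Statistical analysis section is a list of tools. It does not say that the pretest enters only through paired tests, or that the independent test uses follow-up values and not change scores. Logistic regression and path analysis, in the same list, can both carry pretest variables.
- The primary outcome is cessation among women who all smoke at entry. It has no varying pretest value, and logistic regression is its natural method. The ANCOVA variance factor does not transfer to it.
- Only about rho times a baseline difference carries over. Chance imbalance is random error, not bias. Its sampling part is already in the t-test's standard error, and a cluster-valid standard error would cover the between-centre part.
- The figures use self-efficacy, which is not among the listed primary or secondary outcomes.

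All of this stands and limits the point. It could also be said that an article may leave covariates to a fuller plan. That is fair for the logistic model, where no unsuitable method is stated. It does not dispose of the t-tests, because the article positively names them as its methods for means, and its sample size rests on the same unadjusted comparison. Reading the independent test as one on change scores does not rescue it: power is below ANCOVA at every rho in the table, and below the plain follow-up comparison at rho = 0.3.

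**Conclusion.** The point holds for continuous measures that have a pretest value. For these, the named t-tests either give no arm contrast (paired) or, on follow-up values, discard the pretest (independent). The cost is a residual variance larger by 1.10, 1.33 or 1.96 at an assumed rho of 0.3, 0.5 or 0.7. In addition, about rho times any baseline difference remains in the estimate: at rho = 0.5 and an assumed ICC of 0.01 to 0.05, an SD of 0.22 to 0.33 against a target of 1.

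For cessation the point is smaller: name the covariates for a model already listed. No size of gain is shown there. Rho, the ICC and equal centre sizes are assumptions; the power gains ignore clustering and apply to a self-efficacy score. Baseline adjustment is worth making, but it is a separate matter from the four-centre design and does not repair it.

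**What to change.** - **Scores, consumption frequency and number of quit attempts:** make the between-arm analysis a regression of the follow-up value on arm and the woman's own pretest value (ANCOVA, or a repeated-measures model across visits), within whatever model accounts for the four centres.
- **Paired t-tests:** keep them as within-arm description, not as evidence of effect.
- **Cessation:** prespecify pretest smoking frequency and prior quit attempts as covariates in the logistic regression already listed.

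One limit should be stated alongside. The consumption-frequency outcome is restricted to women who did not stop, a group formed after allocation, and adjusting for the pretest does not remove that selection.

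The cost is a change of wording, since the pretest is already planned. The small downside is that the covariates must be fixed in advance.
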